### Team/organizational-level mechanisms

#### Implementation climate measure

Implementation climate will be measured with the Jacobs et al. Implementation Climate Measure [33]. Implementation climate was originally defined by Klein and Sorra (1996) as ‘shared summary perceptions of the extent to which their use of a specific innovation is rewarded, supported and expected within their organization’ [35]. To help researchers quantify the concept, Jacobs et. al. developed a 6-item instrument with two items per construct organized by climate dimension and indicating the degree to which the innovation being implemented is expected, supported, and rewarded in the organization and assessed with a Likert-scale [33]. This measure will be administered to Aim 2 participants at baseline, 3 months, and 6 months.

#### Psychological safety

Psychological safety, the degree to which a team member feels it is safe to take interpersonal risks within the work environment, will be measured using Edmonson’s Psychological Safety Climate [36]. This 7-item measure asks participants to rate responses to each statement on a scale of 0 (doesn’t apply at all) to 4 (entirely applies). Scores are subsequently calculated by averaging item responses. The Psychological Safety Climate Measure will be administered to clinical team members at baseline, 3 months, and 6 months.

#### Intra-organizational alignment

Alignment [12, 15] will be measured based on the degree to which team members from different organizational levels (e.g., physicians, nurses, medical assistants, social workers) exhibit similarity on Edmonson’s Psychological Safety climate [36] and the Jacob’s et al. Implementation Climate Measure [33].

### Team member mechanisms

#### Collaboration and satisfaction about care decisions

The Collaboration and Satisfaction about Care Decisions (CSACD) includes 6 items that measure essential components of collaboration [37]. The instrument was originally created to measure nurse-physician interactions in an intensive care unit, and each item captures a specific aspect of collaboration. Values for each question range from 1 (strongly disagree) to 7 (strongly agree) based on a Likert-type scale. Subscale scores are derived by averaging response values for collaboration (3 questions) and satisfaction (3 questions). The CASCD will be administered to participants at baseline, 3 months, and 6 months to gain insight into communication and coordination as it relates to the depression screening treatment cascade.

#### Card-sorting task (shared mental model)

Card sorting is a research assessment to elicit individual mental models about a participant’s understanding of a situation, event, or process. Within team contexts, card sorting can be used to interrogate the extent to which team members have aligned thinking about key elements of a situation, event or process, i.e., team mental models. Each participant from the Aim 2 trial will complete the card-sorting task following TCT completion to assess team mental models of member roles, responsibilities, and goals across depression care cascade team members.

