Aim 2 will utilize a cluster randomized design in which four specialty care clinics (10 clinicians per clinic; *n* = 40 clinicians) responsible for reviewing and responding to depression screening (youth ages 12–17 years) will be matched and then randomized to a TCT condition (two clinics) versus an early identification universal depression screening condition (two clinics). Clinics will be matched on team size, makeup of the team members, type of medical care focus and then randomized to conditions. Thus, there will be two sets of two matched clinics that will then be randomized, one to the TCT and the other to early identification universal depression screening condition. In the comparison implementation strategy (early identification universal depression screening), multiple discrete strategies will be used including depression screening training in which providers and staff are provided 1) training in the depression screening tool (PHQ), 2) orientation to the clinical pathway (i.e., screening conducted at every urgent care or emergency department visit and every 30 days for all other medical visits), and 3) expectations for handoff to the next step in the care cascade.

The TCT will last 6 months and is proposed to include the following components that will be refined based on Aim 1 findings and developmental activities: Two initial 2-h didactic sessions on effective communication between team members (information-based methods) and simulation exercises based on mock clinical cases (practice-based methods), biweekly performance feedback about intra-team communication in the EHR (demonstration-based methods) provided during regularly scheduled supervision meetings, and a 1 h booster coaching sessions approximately every 2 months over a 6-month period.

#### Specific Aim 3

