### Measures

Multiple measures will be used to assess the outcomes of TCT for Aims 2 and 3. Please refer to Table 2 for a full list of study constructs, outcomes, and the corresponding measures.

**Table 2 Tab2:** Study Constructs and measures (Aims 2 and 3)

Construct		Purpose	Source	Measure	Timepoint
Implementation outcomes	Acceptability, Appropriateness, Feasibility	Outcome	Provider	-Acceptability of Intervention Measure -Intervention Appropriateness Measure -Feasibility of Intervention Measure; Qualitative Interviews	6 mos
	Workflow Efficiency	Outcome	EHR and Provider	-Time from screening to referral via EHR timestamps (referral processing) -Referral to appropriate service (referral quality)	
Team-Level mechanisms	Implementation Climate	Mechanism	Team	Jacobs et al. Implementation Climate Measure [33]	BL, 3 mos., 6 mos
	Intra-Organizational Alignment	Mechanism	Team	Alignment is assessed by the degree to which team members from different organizational levels (e.g., physician, nurse, medical assistant, social worker) exhibit similarity on Psychological Safety Climate and Implementation Climate measures	
Team member-level mechanisms	Communication and Coordination	Mechanisms	Team	Collaboration and Satisfaction About Care Decisions (CSACD)—Collaboration	
	Shared Cognitions	Mechanism	Team	Shared Mental Model via card sorting task	
	Psych Safety	Mechanism	Team	Edmondson’s Psychological Safety Climate	
	Team Indicators	Exploratory	Team	NLP data sources	Monthly; 6 mos
Clinical/service outcomes	Child demographics	Sample characteristics	EHR	Family Demographics Questionnaire	BL, 3 mos., 6 mos
	Clinical outcomes	Outcome	EHR	-Response to elevated depression score -Time (days) to service linkage from elevated depression score	BL, 3 mos., 6 mos
	*Mental Health **Service Linkage*	*Outcome*	*Caregiver*	*-Report of linkage to any mental health service (internal/Rady and external/outside of Rady) following elevated depression score*	*3 mos., 6 mos*
Setting factors	Medical clinic characteristics		EHR and Provider	-# providers -Average patient volume -Patient case-mix: child race/ethnicity, health insurance (public versus private), age	BL

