### Data management

#### Analytic plan

For Aims 2 and 3, we will use multilevel modeling with random intercepts and slopes to test the preliminary effects of TCT on implementation and service outcomes (Aim 2) and mechanisms (Aim 3). Refer to Table 2 for measures of outcomes and mechanisms. Specifically, outcomes include team member-reported acceptability, appropriateness, feasibility and workflow efficiency, and child service outcomes. Potential mechanisms are the proposed mediators of implementation climate, psychological safety climate, communication/coordination, and shared cognitions (see Table 2). Clinic will be included as a covariate (fixed effect). To test the effects of TCT a Group [current implementation vs. TCT] X Time [Baseline, 3, 6 Months] cross-level interaction will be assessed for each outcome. If a statistically significant (*p* < .05) interaction term is evident, simple slopes analyses will be conducted.

Quantitative data and qualitative data will be first analyzed separately. First, quantitative analyses of mechanisms of the TCT implementation strategy will be analyzed using the analytic approach described in Aim 2. To examine the hypothesized mediated effects of implementation strategy condition on implementation and service outcomes, multilevel path analysis will be conducted. Measures of Implementation Climate, Intra-Organizational Alignment, Communication and Coordination, Shared Cognitions, and Psych Safety will be tested as mediators in respective models. The specific mediated effects within these models will be tested using the bias-corrected bootstrap approach [38]. Qualitative interview data will be analyzed using rapid qualitative methods [28] based on a templated summary, deductive approach focused on specified team mechanisms. Specifically, the research team will code transcripts for changes in proposed mechanisms as explanatory factors in implementation and service outcomes. We will then use a mixed-methods analytic approach to synthesize the qualitative and quantitative data collected to examine convergence (i.e., do the two methods confirm or find similar results), complementarity (i.e., do the two methods provide more depth of understanding of research questions), and expansion (i.e., do the two methods provide insights beyond either method alone).

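### The text times the card-sorting task after TCT completion, which conflicts with the three-time-point mechanism analysis and apparently with Table 2; on the text alone, shared cognition has no baseline and its place as a mediator is not established

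*Protocol article*

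**What the plan says.** Three places in the Protocol article bear on when shared cognition is measured.

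- **Card-sorting task (shared mental model).** Each Aim 2 participant "will complete the card-sorting task following TCT completion to assess team mental models of member roles, responsibilities, and goals". No earlier administration is mentioned. Under Specific Aim 2, "The TCT will last 6 months".
- **Measures, Table 2.** Shared cognitions is listed as a mechanism, measured as "Shared Mental Model via card sorting task". In the text available, the timepoint cell of that row is blank. The nearest entry above it, on the implementation climate row, is baseline, 3 and 6 months. The next printed entry below belongs to the team indicators row and is different (monthly and 6 months).
- **Analytic plan.** Mechanisms are analysed with the Aim 2 approach, a multilevel model with random intercepts and slopes and a group-by-time interaction over baseline, 3 and 6 months. In addition: "Measures of Implementation Climate, Intra-Organizational Alignment, Communication and Coordination, Shared Cognitions, and Psych Safety will be tested as mediators in respective models". Clinic enters as a fixed effect.

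**The concern.** The measure-specific sentence gives one occasion at the end of training. The analysis presupposes three, and the table seems to as well. The documents describe shared mental models as a main driver of coordinated team action, and Aim 3 exists to test such mechanisms before a definitive trial.

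If the sentence is followed as written, two things are lost. The first is the pre-training value, which cannot be collected later. The second is the time order that a mediation claim needs. If teams agree more at month 6, that agreement may have produced better workflow or may have resulted from it, and a bootstrap interval for the indirect effect cannot say which.

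**Working it through.** The plan gives no figure on this point, so there is none to reproduce. The check sets the timing statements side by side.

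**1. When is the card sort done according to the text?** TCT runs 6 months and the task follows its completion, so month 6 or later: one stated occasion.

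**2. When is it done according to Table 2?** The row's own cell is blank, so the schedule has to be inferred from a merged cell. The inference can be tested on other blank cells:
- Collaboration measure (blank, same block). Text: "The CASCD will be administered to participants at baseline, 3 months, and 6 months". Agrees.
- Psychological safety (blank, same block). Text: "The Psychological Safety Climate Measure will be administered to clinical team members at baseline, 3 months, and 6 months". Agrees.
- Workflow efficiency (blank, under the 6-month entry of the implementation outcomes block). The text collects it at 6 months. Agrees.

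The implementation climate row, where the entry is printed, also matches its text. Among the directly measured mechanisms, the card sort is the only one whose text departs from the block schedule.

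**3. Number of measurements, before attrition.**
- Table 2 as inferred: 3 × 40 clinicians = 120 card sorts.
- Text: 1 × 40 = 40 card sorts.
- Difference: 120 − 40 = 80, or two per clinician.

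**4. Can the planned model be fitted with one measurement?** No. Time takes a single value, so the group-by-time term and the random slope drop out. Falling back on the group main effect does not help in the model as specified. Each of the four clinics belongs to one arm, so the TCT indicator is the sum of two clinic indicators, and with clinic as a fixed effect it is fully aliased. With three time points the interaction is estimable, because time varies within clinic. This step does not depend on how Table 2 is read.

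**5. Order of mediator and outcomes, if the text is followed.**

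| Outcome | Collected | Card sort (month 6 or later) comes |
|---|---|---|
| Response to elevated score; days to linkage (health record) | baseline, 3, 6 months | after the baseline and 3-month values and after most in-trial events |
| Screening-to-referral time (record timestamps) | 6 months | after most of the events that are timed |
| Reported service linkage | 3, 6 months | after the 3-month report, about the same time as the 6-month report |
| Acceptability, appropriateness, feasibility | 6 months | about the same time |
| Provider-reported referral quality | 6 months | about the same time |

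The mediator is not placed ahead of any of these collections.

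**6. Baseline comparability.** There are two matched pairs, so two clinics per arm. Matching is on team size, team makeup and type of care, not on shared cognition. Without a baseline, a post-training difference between arms mixes any TCT effect with differences that were there before.

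**The case against.** The strongest reply is that this is a condensed article with one loosely worded sentence. The sentence does not say that the card sort is done only once, so a baseline may well be planned. The Table 2 schedule is inferred from a blank cell. Nor is the table a safe authority: it lists child demographics at three time points, while the text collects them at baseline only. A post-only assessment could be the real intention. The trial is also a pilot, and clinics are matched before randomization.

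Much of this stands, and it limits the point. The documents do not show that baseline card sorts will be omitted, and they do not settle which passage governs. What remains is that the stated timing conflicts with the Analytic plan whatever Table 2 means. That is a contradiction in what is written, not a detail left to a fuller document. Matching on other features lessens the baseline problem but cannot remove it with two pairs.

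A reader might infer three stronger things:
- **That the mediator is measured after all its outcomes.** The documents do not support this. The 6-month ratings, referral-quality reports and linkage reports are roughly concurrent with it, and linkage following a late screen could even fall later.
- **That the comparison clinics have no assessment time.** The sentence covers every participant, and the natural reading is a common time near month 6. The wording is loose because those clinics receive no TCT, but this is not a separate defect.
- **That mediation must be redesigned around the 3-month value.** Nothing in the documents requires this, and month 3 is only halfway through the training.

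**Conclusion.** The point holds as an internal contradiction about one measure. The text gives a single card sort at month 6 or later. The Analytic plan needs baseline, 3 and 6 months, and Table 2 appears to give them.

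If the text is followed, one of five named mediators has one measurement instead of three, and the planned group-by-time analysis cannot be carried out for it. A difference between arms cannot be separated from existing clinic differences, and time order for mediation is not established. The other directly measured mechanisms and the primary workflow outcome are not affected.

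The conclusion about Table 2 assumes that blank timepoint cells continue the entry above, which the text confirms for the sibling measures. The conclusions about the model and about mediation do not need that assumption; they assume only that the card sort is given when the text says and at no other time. The contradiction should be resolved before the first TCT session, because a missed baseline cannot be recovered.

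**What to change.** Amend the card-sorting section so that the task is given at baseline (before the first TCT session), 3 months and 6 months, at the same study time points in both arms. Print the schedule on the shared cognitions row of Table 2. Text, table and model then agree.

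The cost is 2 × 40 = 80 further card sorts, which can be added to the surveys already planned at baseline and 3 months. The documents give no task duration, so the respondent time cannot be stated. Repeated sorting may also bring practice effects, or prompt comparison clinicians to think about roles; these should be acknowledged and not assumed equal between arms.

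If a single post-training assessment is intended, correct Table 2, remove shared cognitions from the group-by-time and mediation analyses, and report it as a descriptive 6-month comparison. That costs nothing in data collection but gives up one of the five mediation tests.

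Relating the baseline-adjusted 3-month value to later outcomes is an optional sensitivity analysis.

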#### Team indicators

Team communication data (e.g., transcripts from TCT sessions, inter-provider messages in the EHR) will be collected during the Aim 2 trial. Labels from a subset of the communication data will be generalized to the larger set of unlabeled utterances using a combination of techniques including semi-supervised learning, pre-trained natural language embeddings, and transfer learning. Semi-supervised learning propagates small label sets by making assumptions about the underlying data distribution and distance function. “Embeddings” are mechanisms for mapping high-dimensional spaces to low-dimensions while retaining the most effective representations, making it possible to apply machine learning on large inputs by representing them in the form of a sparse vector. Transfer learning uses classifiers trained on a source domain to classify data in a specific domain. The IN STEP Methods Core NLP team will consult on the identification of language data most useful and appropriate for the assessment of potential language indicators of team effectiveness mechanisms and outcomes in depression screening and engagement in treatment.

### Clinical/service outcomes

#### Demographics

Age, gender, race, ethnicity, education level, primary language, and caregiver working status/profession will be abstracted from the EHR of pediatric patients. This will be collected at baseline.

#### Clinical outcomes

Clinical outcome measures will include responses to elevated depression score and time (in days) to service linkage from elevated PHQ score. This will be measured with data from the EHR at baseline, 3 months, and 6 months.

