**Methods:**

This project aims to refine and test a team communication training implementation strategy to improve implementation of an existing pediatric depression screening protocol in a large pediatric healthcare system. The team will be defined as part of the study but is expected to include medical assistants, nurses, physicians, and behavioral health clinicians within and across departments. The implementation strategy will target team mechanisms at the team-level (i.e., intra-organizational alignment and implementation climate) and team member-level (i.e., communication, coordination, psychological safety, and shared cognition). First, the project will use mixed methods to refine the team training strategy to fit the organizational context and workflows. Next, a hybrid type 3 implementation-effectiveness pilot trial will assess the initial effectiveness of the team communication training (implementation strategy) paired with the current universal depression screening protocol (clinical intervention) on implementation outcomes (i.e., feasibility, acceptability, appropriateness, workflow efficiency) and clinical/services outcomes (increased frequency of needed screening and reduced time to service linkage). Finally, the study will assess mechanisms at the team and team member levels that may affect implementation outcomes.

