### Implementation gaps in depression screening

Effective implementation requires a team of individuals across the cascade to communicate and coordinate in a clear and timely manner. Although system-wide interventions such as universal screening policies and mutual access to EHRs between provider specialties can be facilitative, implementation gaps remain in the depression treatment cascade [11]. For example, not all children are screened, and for those who are screened, timely follow-up and linkage to care in response to elevated scores does not consistently occur. More recent and detailed local data [7] support these implementation gaps. All adolescents screened at risk for moderate-severe depression receive a list of behavioral health self-referral options including internal and external services. However, only internal behavioral health referrals are tracked uniformly at Rady Children’s Health Network.

This project proposes that intra-organizational alignment can serve as a mechanism potentially mediating the association of organizational context (e.g., implementation climate) with implementation outcomes [12–14] (e.g., acceptability, appropriateness) to mitigate gaps in the referral to treatment cascade. This approach is consistent with recent developments in organizational research that consider implementation climate and climate strength, a measure of alignment within groups [15]. However, this study will consider intra-organizational alignment across organizational levels. Integrating team effectiveness approaches with implementation science, such as through coordinated specialty care or collaborative care models, is a promising solution to address gaps related to continuous provider communication and coordinated decision-making about evidence-based depression screening, assessment, and service engagement [16–18].

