### Study objectives

#### Specific Aim 1

Mixed methods will be used to refine a TCT implementation strategy to improve implementation of an existing health system universal depression screening protocol (clinical intervention). We will incorporate organizational team effectiveness research to address implementation challenges associated with health system-wide depression screening protocols. TCT is an effective strategy to enhance communication and decision-making within teams, including in acute healthcare contexts [19–21, 26].

Five focus groups will be conducted with 25 individuals (5 medical specialty clinic leaders, 10 physician or nursing providers, and 10 medical assistants) to identify team (organizational-level) and team member (provider-level) barriers to implementing the existing depression screening protocol. We will also assess workflow efficiency using clinical ethnography and workflow analysis methods [27] to identify specific “pain points” related to screening frequency and time to service linkage. Following rapid analysis [28] of focus group and workflow assessments [27, 29, 30], we will convene a community service working group of pediatric medical specialty clinic and behavioral health care team members to operationalize the components of TCT and tailor for the purposes of increasing the frequency of depression screening and decrease the time to service linkage.

#### Specific Aim 2

A two-arm hybrid type 3 implementation-effectiveness pilot trial will be used to assess the initial effectiveness of the TCT strategy on implementation of the depression screening protocol. The proposed structure and timeline of the TCT is outlined in Table 1. These proposed training components will be refined and finalized based on learnings from the Aim 1 activities with clinic leaders, clinicians, and medical assistants.

**Table 1 Tab1:** Structure and timeline of team communication training

**Team communication training component**	Month 1				Month 2				Month 3				Month 4				Month 5				Month 6			
	1	2	3	4	5	6	7	8	9	10	11	12	13	14	15	16	17	18	19	20	21	22	23	24
Initial training sessions with didactics and simulation exercises (4 h over 2 sessions)	X		X																					
Team performance feedback about intra-team communication in the EHR provided during regular team meetings (15–20 min)		X		X		X		X		X		X		X		X		X		X		X		X
Booster Coaching Sessions (1 h)								X								X								X

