#### Mental health service linkage

This measure will be based on caregiver or patient report of linkage to any mental health service either internal Rady or external/outside of Rady following elevated depression score. Values will be collected at 3 months and 6 months.

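### Response and linkage outcomes exist only for youths with an elevated screen, a group formed after randomisation by a step TCT is designed to change, so their Group x Time contrast may mix speed of care with who is counted

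*Protocol article*

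**What the plan says.** Three places in the protocol article define the youth-level response and linkage outcomes, and all start from an elevated score:

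- The Clinical outcomes section states: "Clinical outcome measures will include responses to elevated depression score and time (in days) to service linkage from elevated PHQ score". These are taken from the EHR at baseline, 3 and 6 months.
- Table 2 repeats the second of these: "Time (days) to service linkage from elevated depression score".
- The Mental health service linkage section covers caregiver or patient report of "linkage to any mental health service either internal Rady or external/outside of Rady following elevated depression score", at 3 and 6 months.

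TCT is also meant to change how many youths are screened. Under Specific Aim 1 a working group will specify TCT and "tailor for the purposes of increasing the frequency of depression screening and decrease the time to service linkage". The hypothesis after Figure 1 and the Discussion repeat this double aim. There is room for change, because the section on implementation gaps says "not all children are screened".

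The Analytic plan tests a Group x Time interaction over baseline, 3 and 6 months. On covariates it says "Clinic will be included as a covariate (fixed effect").

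One further service outcome does not depend on a positive screen. The Abstract names "clinical/services outcomes (increased frequency of needed screening and reduced time to service linkage"), and the Method section says the same. Table 2 gives no measure for screening frequency.

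**The concern.** Response to an elevated score, and days from it, cannot be observed in a youth who was not screened. If TCT brings more youths into screening, the set with an elevated score at 3 and 6 months in TCT clinics may differ from the set that would have been found without it. Randomising clinics does not protect against this, because the selection happens after allocation. The clinic fixed effect removes differences between clinics that stay constant. It does not remove a change over time, within TCT clinics, in who screens positive. That change falls into the Group x Time term, which is read as the effect of TCT.

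The Discussion describes the results as preliminary data for a later definitive test. A strategy that succeeds in screening could appear to slow linkage or to speed it up with no change in the hand-off itself, and that could misdirect the next trial.

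**Working it through.** The documents give no screening coverage, no linkage times and no comparison of screened with missed youths, so the plan has no figure of its own to reproduce here. (The stated power concerns 20 clinicians per arm and is not an input.) Every input in steps 1 to 3 is an assumption; step 4 adds one documented figure.

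**1. General form, with no true effect of TCT on linkage.** Let s0 be the coverage without TCT in the same period and s1 the coverage with it. Let r be the positivity of newly screened youths relative to those screened anyway, and D their difference in mean days to linkage.

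- Share of newly screened youths among screen-positives: w = (s1 - s0)r / [(s1 - s0)r + s0].
- If M0 is the mean for youths screened anyway, the observed mean is (1 - w)M0 + w(M0 + D) = M0 + wD. The false shift is wD.

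With D = 10 days:

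| Coverage s0 to s1 | r | w | False shift |
|---|---|---|---|
| 60% to 80% | 0.5 | 0.10/0.70 = 14% | 1.4 days |
| 60% to 80% | 2 | 0.40/1.00 = 40% | 4.0 days |
| 80% to 90% | 0.5 | 0.05/0.85 = 6% | 0.6 days |
| 80% to 90% | 2 | 0.20/1.00 = 20% | 2.0 days |

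The sign follows D. The shift is 0 if D = 0 or s1 = s0. If control clinics gain the same coverage among the same kind of youth, both arms shift by wD and the contrast is again 0.

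**2. Illustration by severity.** Assume half of true cases are more severe, mean days to linkage are 30 (more severe) and 60 (milder), and care does not change. TCT clinics screen 90% of both groups: the severe share is 0.50 and the mean is 0.50 x 30 + 0.50 x 60 = 45 days.

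- Control screens 90% of severe and 60% of milder cases: the severe share is 0.45/(0.45 + 0.30) = 0.60 and the mean is 0.60 x 30 + 0.40 x 60 = 42 days. TCT looks 3 days slower (3/42 = +7%).
- Control screens 60% of severe and 90% of milder cases: the severe share is 0.30/0.75 = 0.40 and the mean is 0.40 x 30 + 0.60 x 60 = 48 days. TCT looks 3 days faster (3/48 = -6%).

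**3. The two forms agree.** In the first case above, w = 0.15/0.90 = 1/6 and D = 60 - 42 = 18, so wD = 3 days.

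**4. What an all-youth outcome would look like.** The Setting and context section gives 9.9% positive among adolescents screened across the network in 2021. Even with full coverage, about 90.1% of youths could not count as positive and linked. If newly screened youths are positive at the same rate, at most 0.60 x 9.9% = 5.9% can count at 60% coverage and 0.80 x 9.9% = 7.9% at 80%. Screening no longer changes who is in the denominator, but the outcome is diluted and rises with screening as well as with linkage.

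**The case against.** Several objections narrow the point.

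- **Not every service outcome is restricted.** A reader might infer that all service outcomes are computed among elevated screens. Screening frequency is also named and does not depend on a score.
- **Bias is not shown.** A reader might conclude that the arms do compare different youths. That needs a differential change in screening and a difference in newly screened youths; the documents establish neither.
- **The control arm is active.** Under Specific Aim 2 it receives training in the PHQ, the screening pathway and the hand-off, and the text after Figure 1 describes a taskforce that monitors screening compliance. Control screening may rise too, so its case mix cannot be assumed fixed.
- **Room for change may be small.** The Participants section reports high screening rates in specialty services in FY 2023. That favours the lower rows of the table.
- **Covariates are weak ground.** The Analytic plan names clinic and excludes nothing else. A condensed article may leave adjustment to the analysis plan, so the absence of youth covariates is no finding.
- **The outcome is legitimate.** Time from an elevated score needs an elevated score, and it measures the hand-off that the trial targets.

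All of this stands, but it does not remove the core. The conditioning is written into the outcome definitions, and reporting screening frequency separately does not unbias time to linkage.

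**Conclusion.** The point holds as a risk built into the stated definitions, limited to response to an elevated score, time to linkage and reported linkage. Their analysed group is formed after randomisation by a step that TCT is designed to change, and neither the clinic fixed effect nor the Group x Time test removes a shift in who screens positive.

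Size and direction are unknown. Under the assumptions shown, the false difference runs from 0 to about 4 days per 10-day difference between newly screened and otherwise screened youths, in either direction. With coverage already at 80% and rising to 90% it is 0.6 to 2.0 days. For a four-clinic pilot whose estimates feed a later trial, this warrants a supplementary outcome and careful wording, not replacement of time to linkage.

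**What to change.** 1. Alongside the conditional outcomes, add an EHR outcome over all 12-17-year-olds with an encounter at the clinic in each measurement window: screened, positive and linked within a fixed number of days (yes/no), with unscreened youths counted as not linked. Fix the number of days in advance. Include youths whether or not a screen was due or done. Outpatient screening is due only if none was done in the past 30 days, so a denominator of visits with a screen due would itself depend on earlier screening.
2. State that time to linkage among screen-positives is conditional, and interpret it next to screening frequency, which needs a defined measure in Table 2.
3. Compare index PHQ-9 score, age, insurance and language of screen-positive youths by arm and period. Adjust for them as a sensitivity analysis, stating that this reduces selection but does not remove it.

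The cost is a few more EHR fields and an extra table. The Participants section already plans to abstract de-identified youth data on movement through the cascade. Clinic case mix recorded once at baseline will not serve item 3, which needs youth-level values in each period. The all-youth outcome combines the screening and linkage effects and is diluted, because most youths screen negative, so it supplements time to linkage. Taken from the EHR, it would mainly capture internal linkage, since the section on implementation gaps says only internal referrals are tracked uniformly.
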